### **Acknowledgement/ approval of study**

The Investigator will submit this protocol and any related document provided to the subject (such as subject information used to obtain informed consent) to an Ethics Committee (EC) or Institutional Review Board (IRB). Approval from the committee must be obtained before starting the study.

The clinical trial shall be performed in full compliance with the legal regulations according to the Drug Law (AMG - Arzneimittelgesetz) of the Republic of Austria.

An application must also be submitted to the Austrian Competent Authorities (Bundesamt für Sicherheit im Gesundheitswesen (BASG) represented by the Agency for Health and Food Safety (AGES PharmMed) and registered to the European Clinical Trial Database (EudraCT) using the required forms. The timelines for (silent) approval set by national law must be followed before starting the study.

### **Changes in the Conduct of the Study**

#### **Protocol amendments**

Proposed amendments must be submitted to the appropriate CA and ECs. Substantial amendments may be implemented only after CA/EC approval has been obtained. Amendments that are intended to eliminate an apparent immediate hazard to subjects may be implemented prior to receiving CA/EC approval. However, in this case, approval must be obtained as soon as possible after implementation.

#### **Study Termination**

If the sponsor or the Investigator decides to terminate the study before it is completed, they will notify each other in writing stating the reasons of early termination. In terminating the study, the sponsor and the Investigator will ensure the adequate consideration is given to the protection of the subject interests. The Investigator, sponsor or (designated CRO on behalf of the sponsor) will notify the relevant CA and EC. Documentation will be filed in the Trial Master and Investigator Files.

**Clinical Study Report (CSR)**

Within one year after the final completion of the study, a full CSR will be prepared by the sponsor and submitted to the EC and the competent authority.

The Investigator will be asked to review and sign the final study report.

**Insurance**

During their participation in the clinical trial the patients will be insured as defined by legal requirements. The Investigator of the clinical trial will receive a copy of the insurance conditions of the 'patients insurance'. The sponsor is providing insurance in order to indemnify (legal and financial coverage) the Investigator/center against claims arising from the study, except for claims that arise from malpractice and/or negligence. The compensation of the subject in the event of study-related injuries will comply with the applicable regulations. Details on the existing patients insurance are given in the patient information sheet.

**12. Prospective benefits/relevance**

We suppose, that patients with ACS exhibit subclinical signs of 1) disturbed glucose and lipid metabolism, like impaired insulin tolerance, increased visceral fat mass and ectopic hepatic lipid deposition, as well as 2) cardiovascular risk factors, including higher blood pressure, diastolic dysfunction and increased left ventricular septal thickness, as well as 3) changes in chronobiology patterns. Medical restoration of a physiological circadian cortisol rhythm will normalize alterations in the individual chronobiology profile, accompanied by improvements in surrogate parameters of cardiometabolic risk.

Furthermore, the identification of a disease specific chronobiology pattern, which enables to identify even subtle alterations in HPA axis, might offer a novel diagnostic approach to select patients with ACS from non-functioning adrenal incidentaloma. This might help to diagnose patients at risk for adverse effects of unphysiological adrenal cortisol secretion at an early stage, before cardiometabolic and musculoskeletal sequelae develop. The results of this feasibility study might therefore pave the way for future, large interventional studies addressing this promising topic.

**13. Feasibility**

All study related activities will be performed at the Medical University of Vienna. The Division of Endocrinology has a fully equipped biomedical lab and a human research unit (Outpatient Clinic for Metabolic Research i.e. Outpatient Clinic for Metabolic Research “Chiari”). The access to the MR facility for the non-invasive measurements is warranted in the cooperation with [name]. [name] (MR Centre of Excellence) at the Dep. of Radiology, Medical University of Vienna. There is currently a 3 Tesla Magnetom, scanner available at the MR Centre of Excellence. The system is equipped with suitable software and coils. Performance testing of this setup has been performed extensively in several prior studies (16,21,22). Oral glucose tolerance tests will be performed at the Outpatient Clinic for Metabolic Research “Chiari” of the Division of Endocrinology and Metabolism. MR-studies will take place at the centre of excellence of high-field MR of the Medical University of Vienna. Chronobiology surrogates will be analyzed in cooperation with [name], Platform Rhythms of Life, Center for Molecular Biology and [name], Faculty of Psychology, University of Vienna.

#### **14. Additional information:**

**Place of work and cooperation:** This study will be performed as a single center study at the Medical University of Vienna in cooperation of the Division of Endocrinology and Metabolism, Department of Medicine III and the MR Centre of Excellence.

**Time schedule:** All study related activities are planned to be completed within 3 years, starting from 06/2022.

#### **Sample size calculation:**

Up to now there are no studies on hepatic lipid content assessed by H magnetic resonance spectroscopy in patients suffering from autonomous cortisol secretion. Therefore this study has to be considered as a pilot study.

However, evidence from literature and clinical experience suggests that the prevalence of insulin resistance and visceral obesity is increased in this patient population (2). As these factors are both well known to be associated with higher visceral and ectopic fat mass, we estimate that HCL might be about 25% higher in patients with ACS compared to controls. Based on an average HCL of  $5 \pm 2.5$  % fat in a comparable elderly, overweight/obese, sedentary population, which we could observe in our previously

published control population (28) a sample size of 25 patients per group is necessary to detect between group differences to achieve  $\alpha < 0.05$  and  $\beta > 0.80$  in cross-sectional analysis (WPA).

For the interventional part (WPB), we expect a normalization of HCL comparable to the control cohort and therefore a reduction of about 25%. Therefore, a sample size of 15 patients is required to achieve  $\alpha < 0.05$  and  $\beta > 0.80$  in longitudinal analysis.

We expect 2 dropouts in WPA and WPB. These dropouts will be replaced.

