### **Statistical Analysis:**

Data will be presented as means  $\pm$  SD or median (minimum; maximum) depending on normal distribution. Normal distribution will be checked by data visualization and the Kolmogorov-Smirnov test.

Due to the exploratory design of the study, there will be no correction for multiple testing. Due to the exploratory design of the study, there will be no correction for multiple testing.

Hepatic lipid content (HCL) will be considered as primary outcome parameter.

Nullhypothesis: There is no difference in HCL between patients with ACS and the control group.

Alternative hypothesis: There is a difference in HCL between patients with ACS and the control group.

Aim 1: comparisons between the groups of patients with ACS and the control group without ACS will be performed by unpaired student's t-tests. In case of a large distribution of age between the groups, an adjustment by a regression model will be performed.

Aim 2: Comparisons of metric variables between the groups of patients will be performed by unpaired student's t-tests or Mann-Whitney-U tests, depending on normal distribution. Chi-squared test will be used for comparison of discrete variables.

Aim 3: longitudinal analysis before and after treatment will be performed by using paired student's t-tests.

Associations between continuous variables will be described by Pearson's correlation coefficient.

SPSS - Statistics will be used for all computations. Level of statistical significance is set at  $p < 0.05$ .

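### The cross-sectional sample size claims 80% power with 25 patients per group, but its own inputs give about 41%; 80% power would need 64 per group

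*Protocol*

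**What the plan says.** The Sample size calculation in section 14 of the Protocol first notes that no spectroscopy data exist in this population, so the study counts as a pilot. It then gives a power-based justification all the same. For the effect: "we estimate that HCL might be about 25% higher in patients with ACS compared to controls". For the reference value it takes 5 ± 2.5% fat from a control population it regards as comparable. It concludes that "a sample size of 25 patients per group is necessary to detect between group differences" at an alpha below 0.05, with the power target printed as a beta above 0.80. On attrition: "We expect 2 dropouts in WPA and WPB. These dropouts will be replaced".

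The Statistical Analysis part states that HCL "will be considered as primary outcome parameter" and fixes the test: "comparisons between the groups of patients with ACS and the control group without ACS will be performed by unpaired student's t-tests". The hypothesis is non-directional: "Alternative hypothesis: There is a difference in HCL between patients with ACS and the control group". Significance is set at p < 0.05, and age adjustment by regression is planned only if the groups differ widely in age.

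**The concern.** A difference of half a standard deviation is a familiar benchmark for a two-sample t-test, and 25 per group falls well short of what it needs at 80% power. All inputs stand in one paragraph, so the stated size can be checked without any outside source.

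The ACS-versus-control comparison of HCL is the only one for which the Protocol writes out a null and an alternative hypothesis. Anyone relying on the paragraph, such as an ethics committee, a competent authority or a later reader of the results, would take the study as adequately powered for a 25% excess. A non-significant result could then pass as evidence against higher liver fat in ACS, although the design would miss a true excess of the planned size about six times in ten. Section 12 hopes that the results will lead to larger interventional studies, so a misread null result, or a reused calculation, could carry forward.

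A smaller point sits in the same sentence. Beta is the type II error, so a beta above 0.80 literally means power below 20%. The intended meaning is clear, but the notation is wrong.

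**Working it through.** **Inputs, all from section 14 of the Protocol**

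- Control mean 5, SD 2.5 (% fat). The Statistical Analysis part presents data as mean ± SD, so 2.5 is read as an SD. If it were a standard error, the SD would be larger and the power lower.
- ACS mean 25% higher: 5 × 1.25 = 6.25, so the difference is 1.25 points.
- Alpha 0.05, two-sided because the alternative is non-directional.
- Target power 0.80, reading the printed beta as power.
- 25 per group, unpaired Student's t-test, dropouts replaced, so no inflation applies.

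**Attempt to reproduce 25 per group**

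Standardised effect: d = 1.25 / 2.5 = 0.5.

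Normal approximation: n per group = 2 × (1.960 + 0.842)² / d² = 2 × 7.85 / 0.25 = 62.8, so 63. The exact noncentral-t calculation gives 63.8, so **64 per group** (128 in total, against the planned 50). The figure of 25 is not reproduced.

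**Power at 25 per group**

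Noncentrality: d × √(n/2) = 0.5 × √12.5 = 1.77. The critical value of t on 48 degrees of freedom is 2.01. Power is **41.0%** (noncentral t), or 42.4% by normal approximation.

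**What 25 per group can detect with 80% power**

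- Detectable d = 0.809, so a difference of 0.809 × 2.5 = 2.02 points, which is 2.02 / 5 = 40% higher HCL.
- For a 1.25-point difference, the SD would have to be 1.25 / 0.809 = 1.55.

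**Precision**

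Expected 95% confidence interval half-width: 2.01 × 2.5 × √(2/25) = 1.42 points. This exceeds the 1.25-point target. If the sample showed exactly the planned difference and SD, t would be 1.77 and the test would not reach significance.

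**Other readings**

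| Reading | Power at 25 per group | n per group for 80% (normal approximation) |
|---|---|---|
| Two-sided, as planned | 41% | 63 |
| One-sided (not stated in the Protocol) | 54% | 50 |
| ACS SD scales with its mean, 2.5 and 3.125 (assumption) | 33% | 81 |
| Log scale, coefficient of variation 0.5 | 37% | 71 |
| Controls 25% below ACS: 5/0.75 − 5 = 1.67 points | 64% | 36 |
| ACS mean taken as 5, difference 1.0 point | 28% | 99 |
| 23 per group, two dropouts in each group not replaced | 38% | – |

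None gives 25 per group at 80% power. The number 25 appears in only two ways. One is a true difference of 2.0 points: 2 × 7.85 × (2.5/2.0)² = 24.5, rounded up. The other is a one-sided, one-sample formula: (1.645 + 0.842)² / 0.25 = 24.7, which is the same as taking the one-sided two-group answer of 50 per group as the total. Neither matches the stated inputs and design. Where the figure came from cannot be told from the document.

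**The case against.** The strongest defence is that this is a pilot. The sample size section says so, the Statistical Analysis part calls the design exploratory, and section 12 calls it a feasibility study. A pilot needs no power claim, and 25 per group may be a sensible size for one. That stands, and it lowers the consequence of the error. It does not rescue the sentence: having called the study a pilot, the section goes on to claim that 25 per group is needed for a stated alpha and power, and the analysis attaches a formal hypothesis and a significance threshold to that comparison.

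Other objections carry less weight:

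- *Sidedness is implied, not stated.* True. Under a one-sided test the study would be slightly more likely to detect than to miss the effect (54%), but 80% is still far away.
- *Age adjustment could raise power.* It is conditional, and section 5 already plans controls of comparable age and sex. Bringing the residual SD from 2.5 to 1.55 would need covariates that explain 1 − (1.55/2.5)² = 62% of the variance. Nothing in the Protocol suggests this.
- *The Protocol nowhere says that p > 0.05 will be read as no difference.* Correct. That is a foreseeable misreading, not a stated plan.
- *The beta notation is editorial.* Agreed. It adds nothing to the weight of the point.

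**Conclusion.** The concern holds. On the Protocol's own inputs, 25 per group give 41% power for the planned 25% difference in the primary outcome, not 80%. The stated size is 25/64, or about 39%, of what those inputs require. The 41% rests on reading 2.5 as a common SD and on a two-sided test at 0.05, both of which the Protocol supports. The alternative readings tried move power between 28% and 64%, and none reaches 80%. The 33% figure depends on an ACS-group SD that the Protocol does not give and should be read only as sensitivity. The error is in the stated justification. It does not show that 25 per group is wrong for a pilot.

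**What to change.** Keep 25 per group on the pilot rationale already given, and replace the power sentence for working plan A. Suggested text:

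> Working plan A is sized as a pilot with 25 patients per group. With an SD of 2.5% fat and a two-sided alpha of 0.05, this gives 41% power for a difference of 1.25 points (25%) and 80% power for a difference of 2.0 points (40%). The expected half-width of the 95% confidence interval is ±1.4 points.

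Write the target as power, or 1 − beta, in both places where the section now gives beta above 0.80.

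It is also advisable to add one sentence to the Statistical Analysis part: the working plan A conclusion rests on the estimated difference with its 95% confidence interval, and p > 0.05 will not be taken as absence of a difference. This goes beyond correcting the arithmetic, because it shifts the emphasis away from the significance test, but it follows from the low power.

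The cost is Protocol wording and a less favourable power figure, with no extra patients and no change of test. If the sponsor does want 80% power for a 25% difference, the alternative is 64 per group, or 128 − 50 = 78 more patients.

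### The 80% power claimed for 15 metyrapone-treated patients (Working plan B) cannot be reproduced: no SD of within-patient change is stated, and the 25% fall does not follow from normalization (20%)

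*Protocol*

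**What the plan says.** The Protocol's section Sample size calculation takes a control HCL of 5 ± 2.5 % fat from a published control population. For patients with autonomous cortisol secretion (ACS) it adds: "we estimate that HCL might be about 25% higher in patients with ACS compared to controls". For Working plan B it continues: "we expect a normalization of HCL comparable to the control cohort and therefore a reduction of about 25" per cent. It then concludes: "Therefore, a sample size of 15 patients is required to achieve" alpha below 0.05 and power of 0.80 (printed as beta). The two expected dropouts are to be replaced, so the number is not inflated.

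The section Statistical Analysis fixes the test for Aim 3: "longitudinal analysis before and after treatment will be performed by using paired student's t-tests". It sets the significance level at 0.05. The only alternative hypothesis written out concerns the cross-sectional comparison and has no direction: "There is a difference in HCL between patients with ACS and the control group". No sidedness is given for the before-after comparison.

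**The concern.** A paired t-test is governed by the mean change divided by the SD of the within-patient change. The Protocol gives neither that SD nor the correlation between baseline and week 12 from which it could be derived. The quoted 2.5 describes variation between people at one time, which is a different quantity. The sample-size statement therefore lacks the input that determines its answer.

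The assumed effect is also unclear. The text presents 25% as a consequence of returning to the control level, but on the Protocol's own figures that return is 20%. The two readings lead to different sample sizes.

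HCL is the primary outcome and Working plan B is the only interventional part of the trial. A non-significant result read as coming from a comparison with 80% power would carry more weight against metyrapone than the stated inputs can support.

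**Working it through.** **Inputs from the Protocol.** Control mean 5 and cross-sectional SD 2.5 (% fat); ACS excess 25%; 15 patients; alpha 0.05; target power 0.80; paired t-test.

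**Assumptions of this check.** Two-sided test, because the one written alternative for HCL has no direction. SD of 2.5 at both visits. Correlation r between baseline and week 12 from 0.5 to 0.9, shown as a range because the Protocol gives no value.

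**1. The expected fall.**
- ACS mean: 5 × 1.25 = 6.25.
- Normalization: 6.25 − 5 = 1.25 points; 1.25 / 6.25 = 20%.
- A 25% fall: 0.25 × 6.25 = 1.5625 points, ending at 6.25 × 0.75 = 4.69, which is below the control mean.

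**2. Attempt to reproduce 15.** The only stated SD, 2.5, is used as the SD of change. Normal approximation: n = ((z_alpha + z_power) × SD_change / fall)². The exact figures use the noncentral t distribution.

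| Fall | Sides | n, normal approximation | n, exact paired t |
|---|---|---|---|
| 1.25 | two | 32 | 34 |
| 1.5625 | two | 21 | 23 |
| 1.25 | one | 25 | 27 |
| 1.5625 | one | 16 | 18 |

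For example, the second row is ((1.960 + 0.842) × 2.5 / 1.5625)² = 20.1, rounded up to 21. None of the eight figures is 15. The nearest is 16, from a one-sided normal approximation with the 25% fall.

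**3. What 15 patients require.** With n = 15, two-sided alpha 0.05 and the exact paired t, 80% power needs a standardized change (mean change / SD of change) of 0.778.
- Fall 1.25: SD of change at most 1.25 / 0.778 = 1.61.
- Fall 1.5625: SD of change at most 1.5625 / 0.778 = 2.01.

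From SD_change = SD × √(2(1 − r)), it follows that r = 1 − SD_change² / (2 × SD²). With SD = 2.5:
- 1 − 1.61² / 12.5 = 0.79.
- 1 − 2.01² / 12.5 = 0.68.

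**4. Power with 15 patients over the assumed range.**

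| r | SD of change | Power, fall 1.25 (20%) | Power, fall 1.56 (25%) |
|---|---|---|---|
| 0.5 | 2.50 | 44% | 62% |
| 0.6 | 2.24 | 52% | 71% |
| 0.7 | 1.94 | 64% | 83% |
| 0.8 | 1.58 | 81% | 94% |
| 0.9 | 1.12 | 98% | >99% |

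**The case against.** **The study calls itself a pilot and exploratory.** It does, and this lowers the seriousness. It does not cover the sentence at issue, which says that 15 patients are required to reach a stated alpha and power. A pilot can justify 15 on feasibility or precision, but an 80% claim still needs its inputs.

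**The 20% versus 25% mismatch may be loose wording.** The text says about 25%, and if the percentage is a share of the control mean, the excess and the fall are the same 1.25 points. That reading is possible, and it is why the mismatch comes second here. Read literally, however, a reduction is relative to the starting value, and the choice moves the two-sided number from 23 to 34 when the SD of change is 2.5.

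**The correlation may well be high.** It may, and then 15 is enough: from about 0.79 for the smaller fall, or about 0.68 for the larger. The Protocol neither states nor sources such a value, and it says that no spectroscopy studies of HCL in ACS exist.

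**A stronger reading is tempting:** that 15 is simply too few, or that the true power is near one half. The Protocol does not support this. Power near one half applies only to the 1.25-point fall with a correlation of roughly 0.5 to 0.6, and nothing in the Protocol favours those correlations over 0.8 or 0.9.

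**Conclusion.** The point holds as a claim that cannot be verified, not as a sample size shown to be wrong. The main defect is the missing SD of within-patient change, without which 80% power for 15 patients does not follow from anything in the Protocol. The secondary defect is that the 25% reduction is presented as following from normalization, which on the Protocol's own figures is 20%.

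Over the assumed correlations of 0.5 to 0.9, power lies anywhere between 44% and more than 99%, depending also on which fall is meant. That range rests on a two-sided test and an SD of 2.5 at both visits; neither is stated for Working plan B.

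This should be fixed but is not critical: the trial is a declared pilot, and the test, endpoint and conduct are unaffected. A reader might infer that the correction would make a null result informative about metyrapone. It would not do so by itself, because the open-label single-arm design sets its own limit.

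**What to change.** In the section Sample size calculation:

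1. Correct the expected reduction to about 20% (1.25 points, from 6.25 to 5), or keep 25% and justify a fall to below the control mean.
2. State the assumed SD of the within-patient change (or the correlation with the SD at each visit), its source, and whether the test is two-sided; then recompute.
3. If no source exists, replace the 80% claim with wording such as: n = 15 gives 80% power (two-sided alpha 0.05) for a mean change of 0.78 SD of the within-patient change; this corresponds to a 1.25-point fall only if that SD is at most 1.61.

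The cost is a change of protocol wording. The number of patients can stay at 15, and neither visits nor analysis change.

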### **Statistical Analysis:**

Data will be presented as means  $\pm$  SD or median (minimum; maximum) depending on normal distribution. Normal distribution will be checked by data visualization and the Kolmogorov-Smirnov test.

Due to the exploratory design of the study, there will be no correction for multiple testing. Due to the exploratory design of the study, there will be no correction for multiple testing.

Hepatic lipid content (HCL) will be considered as primary outcome parameter.

Nullhypothesis: There is no difference in HCL between patients with ACS and the control group.

Alternative hypothesis: There is a difference in HCL between patients with ACS and the control group.

Aim 1: comparisons between the groups of patients with ACS and the control group without ACS will be performed by unpaired student's t-tests. In case of a large distribution of age between the groups, an adjustment by a regression model will be performed.

Aim 2: Comparisons of metric variables between the groups of patients will be performed by unpaired student's t-tests or Mann-Whitney-U tests, depending on normal distribution. Chi-squared test will be used for comparison of discrete variables.

Aim 3: longitudinal analysis before and after treatment will be performed by using paired student's t-tests.

Associations between continuous variables will be described by Pearson's correlation coefficient.

SPSS - Statistics will be used for all computations. Level of statistical significance is set at  $p < 0.05$ .

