##### **Secondary outcome parameters:**

- insulin secretion and sensitivity based on validated indices (HOMA\_IR, CLIX)
- subcutaneous and visceral fat mass, body composition
- Systolic and diastolic heart function, epicardial and pericardial fat mass
- ectopic lipid deposition in the skeletal muscle and the myocardium
- standardized blood pressure measurements (blood pressure for 24h hours and Schellong tests)
- parameters of systemic inflammation (CRP, IL-6, PAI-1, TNF-alpha, homocysteine, leucocytes, monocytes)
- parameters of the Renin-Angiotensin-Aldosterone system (RAAS) activation (RAAS FINGERPRINT®) (18)

- hypercoagulability assessment by thrombin generation assays (TECHNOTHROMBIN ®)
- standardized clinical chronotype evaluation by Munich ChronoType Questionnaire and psychological testing
- body temperature measurements during the day by an actimetry watch
- analyses of peroxiredoxin oxidation cycles from red blood cells (19),
- circadian clock transcript changes from peripheral blood mononuclear cells (20),
- combined untargeted/targeted LC-MS/MS based approaches
- concentrations of testosterone and adrenal androgen precursors
- gender specific differences

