## **5. Methods:**

### **Study design:**

#### **Working plan A (WPA):**

#### **Cardiometabolic phenotyping:**

To address aim 1 we will perform a cross-sectional study in patients, who are in routine care at the endocrine outpatients' clinic for the hormonal work up of an adrenal adenoma. 25 patients with an ACS will be recruited and compared to 25 patients of comparable age and sex with a sufficient suppression of cortisol  $< 1.8$  ug/dl following a 1 mg dexamethasone suppression test.

Experiments will be performed in the morning after an overnight fast. Subjects have to avoid intense physical exercise and consumption of alcoholic beverages for at least 48 hours previous to study related experiments.

$^1\text{H}$  magnetic resonance (MR) spectroscopy measurements will be performed in high field 3T whole body MR system (Magnetom, Siemens Healthcare, Erlangen, Germany) equipped with appropriate surface coils. Ectopic fat in the liver, the skeletal muscle and the myocardium will be assessed by the single voxel localized  $^1\text{H}$  MRS method (41).

After the MR measurements a frequently sampled oral glucose tolerance test will be performed and surrogate parameters of insulin secretion and sensitivity will be

calculated based on validated indices (HOMA\_IR, CLIX, OGIS, IGI, Disposition Index, Adaptation Index) (21).

Additionally, blood will be drawn at baseline for the measurement of parameters of systemic inflammation (CRP, IL-6, PAI-1, TNF-alpha, homocysteine, leucocytes, monocytes), the renin-angiotensin-aldosterone system (RAAS FINGERPRINT ®) and hypercoagulability (TECHNOTHROMBIN ®).

To estimate diurnal cycles of cortisol secretion salivary cortisol will be drawn at 8:00 a.m. and midnight.

To address aim 2, additional blood will be drawn to analyze the peroxiredoxin oxidation cycles from red blood cells (19), as well as the circadian clock transcript changes from peripheral blood mononuclear cells (21).

In addition, blood will be stored for combined untargeted/targeted LC-MS/MS based metabolomic/proteomic approaches.

Overall, 125 ml blood will be drawn in total for all biochemical analyses of WPA.

A systematical assessment of the chronotype will be performed by using the Munich ChronoType Questionnaire. Furthermore, the following psychological tests will be applied:

- Measurement of vigilant attention and impulsivity (by means of the Psychomotor Vigilance Task)
- Implicit association of concepts (by the Implicit Association Test)

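### The unconditional no-correction rule also covers the untargeted LC-MS/MS outcome, leaving the share of false hits in that feature list uncontrolled

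*Protocol*

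**What the plan says.** The Statistical Analysis section of the protocol says, in a sentence printed twice: "Due to the exploratory design of the study, there will be no correction for multiple testing". It adds one threshold for everything: "Level of statistical significance is set at" p < 0.05. No class of outcome is excepted, and no false-discovery rate or separate rule for high-dimensional data is given.

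The list of secondary outcome parameters includes "combined untargeted/targeted LC-MS/MS based approaches". The methods for working plan A specify the scope: "blood will be stored for combined untargeted/targeted LC-MS/MS based metabolomic/proteomic approaches". Under working plan B, the measurements of working plan A are made in 15 treated patients at baseline and again at 12 weeks.

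The tests are set out variable by variable. For Aim 2: "Comparisons of metric variables between the groups of patients will be performed by unpaired student's t-tests or Mann-Whitney-U tests". Aim 1 uses unpaired t-tests and Aim 3 paired t-tests. The cross-sectional comparison is small: "25 patients with an ACS will be recruited and compared to 25 patients of comparable age and sex".

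The protocol calls itself exploratory and a pilot, and names hepatic lipid content as its single primary outcome.

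**The concern.** Omitting a correction is a reasonable choice when a pilot reports a limited set of outcomes that were named in advance, because the reader can count them and discount accordingly. An untargeted screen is different. Its product is a list of whatever crossed the threshold, and the list is useful only if one knows roughly what fraction of it is false. A per-feature threshold of p < 0.05 does not control that fraction, which depends on how many features are screened and how many truly differ. The protocol describes no validation cohort or replication step that would filter the list later.

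This is not a detail left open for a statistical analysis plan. The protocol rules correction out for all tests, so an analysis plan that used false-discovery control for these data would depart from the protocol as written.

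**Working it through.** **Inputs from the protocol.** The per-test level is 0.05 with no correction. The cross-sectional comparison is 25 v 25 and the before-after comparison has 15 pairs. The test is taken as two-sided, because the alternative hypothesis for the primary outcome is non-directional ("There is a difference in HCL between patients with ACS and the control group"). The protocol states no family-wise error rate, false-discovery rate or feature count, so there is no figure of its own to reproduce.

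**Assumption.** The number of null features, m, is taken as 200 to 2,000.

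**Step 1: expected false positives.** The expected count is 0.05 × m for each comparison. It does not depend on the sample size or on correlation between features. The 95% ranges and the chance of at least five are binomial and assume independent features.

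| m | Expected false positives | 95% range | Chance of at least five |
|---|---|---|---|
| 200 | 0.05 × 200 = 10 | 4 to 16 | 0.97 |
| 1,000 | 0.05 × 1,000 = 50 | 37 to 64 | about 1 |
| 2,000 | 0.05 × 2,000 = 100 | 81 to 120 | about 1 |

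The before-after comparison has the same expectation again.

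**Step 2: correlation.** The comparison of 25 v 25 was simulated with m = 500 null features and 1,000 runs per structure. The expected count is 0.05 × 500 = 25.

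| Structure | Mean | Median | 95% range | At least one, uncorrected | At least one, Benjamini-Hochberg 5% |
|---|---|---|---|---|---|
| Independent | 24.8 | 25 | 16 to 35 | 1.00 | 0.051 |
| Blocks of 10, correlation 0.5 | 24.9 | 25 | 13 to 40 | 1.00 | 0.042 |
| Blocks of 50, correlation 0.8 | 24.9 | 19 | 0 to 80 | 0.97 | 0.026 |
| Common correlation 0.3 | 23.7 | 17 | 5 to 84 | 1.00 | 0.031 |
| Common correlation 0.6 | 25.7 | 6 | 0 to 179 | 0.90 | 0.022 |

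The mean stays near 25 throughout. The spread does not: in the last row, fewer than five false positives occur in about 44% of runs (1 − 0.559).

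**Step 3: false share of the list.** Let π be the proportion of features that truly differ, all by the same standardised difference d. Then the false share = 0.05(1 − π) / [0.05(1 − π) + π × power]. At 25 per group, the t-test power is 0.410 for d = 0.5 and 0.934 for d = 1.0.

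- π = 5%, d = 0.5: 0.0475 / (0.0475 + 0.05 × 0.410) = 0.70
- π = 5%, d = 1.0: 0.0475 / (0.0475 + 0.05 × 0.934) = 0.50
- π = 10%, d = 0.5: 0.045 / (0.045 + 0.10 × 0.410) = 0.52
- π = 10%, d = 1.0: 0.045 / (0.045 + 0.10 × 0.934) = 0.33

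These shares apply to the 25 v 25 comparison only. The share for the 15 pairs would need a within-patient standard deviation for the features, which the protocol does not give.

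**The case against.** The strongest case against the point is that the study openly calls itself an exploratory pilot, that this is one item among about 15 secondary outcomes, and that blood is only to be stored for these assays. No omics workflow is described, so feature-by-feature testing is inferred from the general test rules. False-discovery control could also be applied at reporting without changing what is collected. Most of this stands and keeps the point minor. It does not remove it, because the rule is worded without exception and the only tests the protocol describes are variable by variable.

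A reader might infer three stronger things that the documents do not support.

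- **That the rule guarantees many false positives, or a list made up largely of chance hits.** The feature count is not stated, and with strong correlation few or no false positives can occur. Whether most hits are false depends on how many features truly differ; the calculated share runs from 33% to 70%.
- **That false disease-specific markers would be declared and a diagnostic tool built on them.** The protocol attaches both ideas, in hedged terms, to the chronobiology pattern of Aim 2. The LC-MS/MS sentence stands in a separate paragraph and is assigned to no aim.
- **That the clock transcripts need the same correction.** They are a named, hypothesis-driven measure with no stated panel size, and nothing in this argument separates them from the other named secondary outcomes.

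**Conclusion.** The point holds in a limited form. The protocol's no-correction rule reaches an untargeted metabolomic and proteomic screen in two comparisons, and under that rule the false share of the resulting list is uncontrolled. On the assumption of 200 to 2,000 null features tested one at a time, the average is about 10 to 100 false positives per comparison, with wide variation if features are correlated. In the 25 v 25 comparison, roughly a third to 70% of hits would be false if 5-10% of features truly differ at d = 0.5 to 1.0. The feature count, the true proportion and the effect sizes are all assumptions.

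Severity is minor. The primary outcome is untouched, and omitting correction for the other named secondary outcomes remains acceptable.

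**What to change.** Limit the no-correction statement in the Statistical Analysis section to the other named secondary outcomes, and add:

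*For untargeted LC-MS/MS features, Benjamini-Hochberg false-discovery-rate control (for example 5-10%) is applied within each platform and comparison, q-values are reported, and findings are labelled hypothesis-generating.*

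In the simulations with 500 null features, this procedure at 5% lowered the chance of declaring any feature from 0.90-1.00 to 0.02-0.05. It suits exploratory work because it calibrates the list without demanding confirmatory rigour. The cost is a sentence or two in the protocol and fewer nominal hits reported, some of which may be true. Recruitment, sampling and the primary analysis do not change.
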